**STUDY SUMMARY**

**Purpose:** To conduct an individual participant data (IPD) meta-analysis of prospective HIV prevention studies to evaluate prevalence and incidence of sexually transmitted infections (STIs) and bacterial vaginosis (BV) among women in sub-Saharan Africa

**Design:** Meta-analysis of individual participant data from 18 prospective HIV prevention studies using both one- and two-stage meta-analysis approaches.

**Study Population:** Approximately 37,000 women from clinic and community populations and groups of women at high-risk of HIV infection enrolled in selected prospective studies in sub-Saharan Africa.

**Primary Objectives:** 1) To evaluate the prevalence of selected

STIs/BV among women in sub-Saharan Africa by region, population type, and other pre-specified characteristics.

2) To evaluate the incidence of selected

STIs among women in sub-Saharan Africa by region, population type, and other pre-specified characteristics.

**Secondary Objectives:** 1) To evaluate the prevalence and incidence of co-

infections among the STIs/BV.

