**2. OBJECTIVES**

Using individual level data from the 18 prospective, longitudinal studies included in the HC-HIV meta-analysis dataset, we will estimate the prevalence and incidence of selected STIs/BV among women in sub-Saharan Africa and investigate potential differences by region, population type, and demographic characteristics.

Specifically, we will investigate the following objectives:

1. To evaluate the prevalence of selected STIs (chlamydia, gonorrhea, trichomoniasis, syphilis, and HSV-2) and BV among women in sub-Saharan Africa by region, population type, time period, age, and pregnancy status.
   1. To evaluate the prevalence of co-infections among the STIs/BV
2. To evaluate the incidence of selected STIs (chlamydia, gonorrhea, syphilis, trichomoniasis,and HSV-2) among women in sub-Saharan Africa by region, population type, time period, and age.
   1. To evaluate the incidence of co-infections among the STIs

The term “STIs/BV” may refer to up to 6 conditions: gonorrhea, chlamydia, syphilis, trichomoniasis, HSV-2, and/or BV. For each objective, the precise conditions included were determined by the biological/ epidemiological basis for the particular research question, the availability of STI/BV-specific data at different time points, the validity of combining test results across studies or of calculating incidence for a given condition, and other methodological and biological considerations. See Section 3.3 for more details. Human papillomavirus (HPV) is not included as the majority of studies did not include HPV data.

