Region (based on geographical location of the study) will be defined as South Africa, Eastern Africa (Kenya, Uganda, Tanzania, Rwanda), or Southern Africa (Zambia, Zimbabwe, Malawi, Botswana). Population types (based on overall study population enrolled) will be defined as higher-risk or clinic/community-based populations. Higher-risk populations include studies where participants were recruited from bars or other recreational facilities like guesthouses and hotels, or were women who engage in transactional sex. Clinic/community-based populations include participants recruited in a clinic setting, such as a family planning/reproductive health clinic, as well as studies where participants were recruited from the general population or community. Some studies in the HC-HIV meta-analytic dataset recruited HIV-negative partners in HIV-discordant couples. Although these participants may be at higher risk for HIV transmission than the general population, their risk for STI/BV may be similar to clinic/community-based populations given that they are in a stable relationship. These studies will initially be analyzed separately, STI/BV specific estimates reviewed, and if appropriate (based on comparison with estimates from other populations), will be included in either the higher-risk strata or the clinic-based strata. If not appropriate, estimates from these studies will be presented separately. See Appendix Table 1 for proposed classifications of studies according to these two characteristics.

Time period, age, and pregnancy status will be based on individual participant characteristics. Time period will be categorized as participants whose baseline data were collected prior to 2002 (“earliest” time period), participants whose baseline data were collected during 2003 to 2006 (“later” time period), and participants whose baseline data were collected in 2007 or later (“latest” time period). The categorization of time periods may be adjusted if necessary based on available sample size. Age will be categorized as 15-49 years, 15-24 years, 25-49 years, and if possible given sample size, 15-19 years, and 20-24 years. The categorization of age may be adjusted if necessary based on available sample size. Pregnancy status will be based on pregnancy status at baseline, either self-reported or by pregnancy test.

To the extent possible given sample size, prevalence and incidence estimates will be cross-stratified by various characteristics.

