**5.2.1 Two-stage meta-analysis**

We will use two-stage meta-analysis as our primary approach to examine prevalence and incidence estimates. Using this method, participants in each study are compared directly only with other participants in the same study. The two-stage method is well suited to assess between study heterogeneity. While the method is less suitable for identifying prognostic factors (due to the different sets of covariates measured across datasets), it is possible to assess effect modification.

In the first stage, IPD in each study are analyzed separately to obtain summary statistics. We will use binomial regression models to estimate prevalence estimates for each selected STI/BV and Poisson regression to estimate the incidence for each selected STI.

If appropriate, the second stage is to use standard meta-analysis techniques to combine the summary measures to give an overall estimate of prevalence and incidence across studies by population-type. The decision to combine results and conduct further analyses using random and/or fixed effect models depends on the level of between-study heterogeneity.

The same approach will be used to estimate prevalence and incidence for each stratum of interest based on region, population type, age, pregnancy status, and time period of the study.

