**5.3. Study limitations and sensitivity analyses**

Though this meta-analysis provides high quality individual participant data and valuable information about the prevalence and incidence of selected STIs/BV, our approach has some limitations. First, the validity of the results of the meta-analysis is dependent on the quality of the individual component studies. While the IPD meta-analysis can help avoid problems associated with the analyses and reporting of the component studies, it cannot eliminate bias due to their study design or conduct. For example, studies which recruited high-risk women will likely have higher incidence estimates. In addition, due to the variety of study designs, not all stratification subgroups may be available in all component studies. Second, as the HC-HIV meta-analysis dataset is a convenience sample of prospective longitudinal studies that were identified for an analysis of hormonal contraception and the risk of HIV acquisition, the studies included may not be representative of all populations in the regions of interest for the STI/BV analysis. Finally, it is also possible that we may be unable to recode variables appropriately across studies and may not be able to investigate all sub-classifications of interest.

We will perform the following sensitivity analyses to examine the robustness of the results of our meta-analyses:

1. Based on the type of diagnostic criteria – stratify and analyze data/studies by the following criteria :
2. For chlamydia and gonorrhea: any test vs. NAAT only
3. For BV: any test vs. Nugent/Ison-Hay only
4. Based on the assessment of the risk of bias of the component study – stratify studies with and without an identified risk of bias. Suggested stratification for incidence estimates: studies that have retention rates <80% at one year vs. studies that have ≥80% retention
5. Based on intervention arm – repeat incidence analysis excluding all intervention arms.
6. Based on length of follow-up – for calculation of incidence, stratify studies with short versus longer follow-up time periods. Suggested stratification: ≤3 months vs 3 or more months followup
7. Based on study inclusion criteria – remove studies that included diagnosis with a specific STI for study inclusion for investigation of the prevalence and incidence of other STIs (if resources allow)
8. Based on censoring criteria – for calculation of incidence do not censor at first diagnosis of STI in question (if resources allow)

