**Table 1. Studies included in the HC-HIV meta-analysis dataset**

| Study  # | PI | Country | Region category | Study Population | Study population category | Study design/objective | Ages included | Included  *N* |
| --- | --- | --- | --- | --- | --- | --- | --- | --- |
| 1 | [name] | Kenya (Mombasa) | Eastern Africa | Women who engage in transactional sex | High-risk | Cohort: hormonal contraception and HIV | 16-48 | 1,270 |
| 2 | [name] | South Africa | South Africa | Women not screened for cervical cancer | Clinic/  community-based  population | RCT: cervical cancer screening interventions | 35-49 | 4,160 |
| 3a | [name] | Uganda | Eastern Africa | Women attending RH clinics | Clinic/  community-based  population | Cohort: hormonal contraception and HIV | 18-35 | 2,201 |
| 3b | [name] | Zimbabwe | Southern  Africa | Women attending RH clinics | Clinic/  community-based  population | Cohort: hormonal contraception and HIV | 18-35 | 2,248 |
| 4 | [name] | Kenya | Eastern  Africa | Women who engage in transactional sex | High-risk | RCT: presumptive antibiotic treatment | 18-49 | 414 |
| 5 | [name] | Tanzania | Eastern  Africa | Women working in bars | High-risk | Cohort: microbicide feasibility study | 15-49 | 978 |
| 6 | [name] | Tanzania | Eastern  Africa | Women working in bars and other recreational facilities | High-risk | RCT: HSV suppression to reduce HIV transmission | 16-35 | 781 |
| 7a | [name], [name] | Zimbabwe  (MIRA) | Southern  Africa | Sexually active women | Clinic/  community-based  population | RCT: diaphragm/ condoms to reduce HIV acquisition | 18-49 | 2,455 |
| 7b | [name], [name] | South Africa  (MIRA) | South Africa | Sexually active women | Clinic/  community -based  population | RCT: diaphragm/ condoms to reduce HIV acquisition | 18-49 | 2,493 |
| 8 | [name], [name] | South Africa  (PALESA) | South Africa | Women attending RH clinics | Clinic/  community-based  population | Cohort: hormonal contraception and HIV | 18-41 | 551 |
| 9 | [name] | South Africa  (RHRU) | South Africa | Women attending clinics | Clinic/  community-based  population | Cohort: microbicide feasibility study | 18-35 | 694 |
| 10 | [name] | South Africa | South Africa | Women attending clinics | Clinic/  community-based  population | Cohort: microbicide feasibility study | 15-49 | 261 |

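### Stratum levels pooled separately do not give the within-study comparison that Section 5.2.1 claims, so age, pregnancy and period differences can mix within- and between-study variation

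*Protocol*

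**What the plan says.** Section 2 sets out to estimate prevalence and incidence and to "investigate potential differences by region, population type, and demographic characteristics". Section 5.2.1 makes two-stage meta-analysis the primary approach and says that with it "participants in each study are compared directly only with other participants in the same study". The first stage is then defined: "We will use binomial regression models to estimate prevalence estimates for each selected STI/BV and Poisson regression to estimate the incidence". No prevalence ratio, rate ratio or odds ratio within a study is named. For strata, Section 5.2.1 continues: "The same approach will be used to estimate prevalence and incidence for each stratum of interest". Section 3.6 places three of the stratifiers at the level of the woman: "Time period, age, and pregnancy status will be based on individual participant characteristics". Section 5.3 concedes that "not all stratification subgroups may be available in all component studies", but draws no consequence for comparing strata. In Table 1, Study 2 is listed as "RCT: cervical cancer screening interventions | 35-49 | 4,160".

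**The concern.** The property claimed in Section 5.2.1 belongs to a two-stage analysis whose first stage is a contrast within each study. It does not belong to one whose first stage is a level. If the 15-24 estimate comes from one set of studies and the 25-49 estimate from another, their difference reflects age and also which sites, recruitment settings and test types supplied each stratum. A reader told that the method compares women only within their study would take the difference as a participant-level one. The prevalence and incidence levels, which are the main output, are not at issue. What is at stake is any statement that one age group, or pregnant women, or a period has more infection than another.

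**Working it through.** **1. The plan's own total.** The Study Summary gives "Approximately 37,000 women from clinic and community populations" and other groups as the population. Summing the included N over the 26 rows of Table 1 gives 37,681, which is 681/37,000 = 1.8% above the stated figure. The table and the text agree.

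**2. Which rows can supply each age stratum.** Taking the lower age limits in Table 1, the only row that starts above 24 is Study 2 (35-49). The other 25 rows can in principle supply both 15-24 and 25-49.

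- Share of the whole dataset: 4,160/37,681 = 11.0%.
- South Africa clinic/community rows (2, 7b, 8, 9, 10, 12, 16d, 17, 18b): 4,160 + 2,493 + 551 + 694 + 261 + 5,567 + 5,654 + 444 + 639 = 20,463. Share: 4,160/20,463 = 20.3%.

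Nesting age within region and population type (Section 3.6) therefore raises Study 2's share. In addition, six rows (3a, 3b, 6, 9, 18a, 18b) stop at age 35, so the 25-49 stratum covers different ages in different studies.

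**3. Which outcomes Study 2 touches.** Table 3, which is marked as still to be updated, shows no HSV-2 or syphilis data and no follow-up chlamydia or gonorrhea tests. Its trichomoniasis test is wet mount, which Section 3.4 excludes from incidence. Its gonorrhea test is hybrid capture, which Section 3.4 does not list for gonorrhea. That leaves chlamydia and trichomoniasis prevalence, plus BV prevalence if the tested subset meets Section 3.2. No incidence estimate is affected.

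**4. Size, simple form (assumed values).** Assume an older-stratum prevalence of 0.08 in k studies, a true within-study prevalence ratio of 1.5 (so 0.12 in the young), and one further study in the older stratum only, at 0.04 or 0.12. Pool logits with equal weight. The logits of 0.08, 0.04 and 0.12 are -2.442, -3.178 and -1.992.

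- k=8, extra study 0.04: (8 × -2.442 - 3.178)/9 = -2.524, or 0.0742; ratio 0.12/0.0742 = 1.62.
- k=8, extra study 0.12: (8 × -2.442 - 1.992)/9 = -2.392, or 0.0838; ratio 1.43.
- k=3: ratios 1.78 and 1.35.

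With nine studies the error is about -5% to +8%. Nine rows is an upper bound for this stratum, because Section 3.2 selects studies infection by infection.

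**5. Size with the Table 1 sample sizes (assumed prevalences).** Nine South Africa clinic/community rows; prevalence 12% in all but Study 2; 45% of women under 25 in the other eight; no true age effect. Fixed-effect weights are n·p·(1-p). With Study 2 at 6%, the eight rows weigh 16,303 × 0.55 × 0.12 × 0.88 = 947 and Study 2 weighs 4,160 × 0.06 × 0.94 = 235. The older logit shifts by (-2.752 + 1.992) × 235/1,182 = -0.151, so the apparent OR is exp(0.151) = 1.16.

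| Study 2 prevalence | Fixed effect | Random effects (DerSimonian-Laird) |
|---|---|---|
| 12% | 1.00 | 1.00 |
| 9% | 1.09 | 1.06 |
| 6% | 1.16 | 1.10 |
| 3% | 1.18 | 1.19 |

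With a true OR of 2.00, random effects give 2.11, 2.20 and 2.38 at 9%, 6% and 3%. Pooling within-study contrasts returns 1.00 or 2.00, because Study 2 drops out.

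**6. What drives the error.** These are simulations with no true effect.

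- Same studies in both strata, but 20-70% of women under 25 and a between-study SD of 0.5 on the logit scale: the apparent OR lies in 0.96-1.05 in 95% of runs. Unequal random-effects weights alone do little harm.
- Fully separate sets, three studies of 1,000 against three: the 95% range is 0.62-1.60 at SD 0.3, 0.46-2.17 at SD 0.5 and 0.28-3.45 at SD 0.8.

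The second case is the extreme that period could approach, and pregnancy too if pregnant women come from few studies. The protocol gives neither enrolment dates nor pregnancy counts by study, so it does not show how close either comes.

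**The case against.** The best defence is that no contrast is planned. The numbered objectives in Section 2 are levels by stratum, and Table 5 lists stratum estimates and heterogeneity statistics, with no ratio or test between strata. The text also holds partial safeguards:

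- Section 3.6 explores age, period and pregnancy within region and population type.
- Section 5 mentions multivariable methods, and Section 5.2.1.a allows meta-regression.
- Section 5.2.1 itself calls the two-stage method less suited to prognostic factors.
- Section 5.2.2 puts study identity in the one-stage model and says such models can handle patient-level covariates; Table 5 ticks a one-stage analysis for every stratum.
- Section 5.3 admits uneven subgroup availability and the authors promise cautious interpretation.
- Covariate terms and centring are details that a statistical analysis plan could supply.

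Much of this stands. A reader might infer that between-study differences will be mistaken for participant-level ones and that within-study information is lost. The protocol does not support that: no between-stratum test is written, and nearly every row can supply both age groups. A lower prevalence in Study 2 could also be partly a true age effect, since all its women are 35 or older.

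The safeguards still do not cure the point. The one-stage models are specified only for overall prevalence and incidence, name no age, pregnancy or period term, and are said to be possibly invalid under marked heterogeneity. Meta-regression on study characteristics is itself a between-study comparison. And the issue is not only omitted detail: Section 5.2.1 fixes the quantity as stratum levels while crediting them with a property that they lack.

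**Conclusion.** The point holds in a limited form. Investigating differences is a stated aim, and the specified method does not make the within-study comparison that Section 5.2.1 describes. For age, the documented exposure is one row of 26. It bears mainly on chlamydia and trichomoniasis prevalence in South African clinic/community women (and BV if its subset qualifies). On assumed prevalences the distortion is modest: 1.43 to 1.62 against a true 1.5 with nine studies, and none if Study 2 has the same prevalence as the other studies. For pregnancy the mechanism is the same but its size is unknown.

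For period, a reader might infer that individual data always allow an unconfounded within-study contrast. They do not. Such a contrast needs studies that enrolled across a period boundary, and the protocol gives no enrolment dates. Even for age and pregnancy, a within-study ratio removes confounding between studies only; confounding among women within a study remains.

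**What to change.** - Keep the stratum estimates as descriptive results, and reword Section 5.2.1 so that it does not claim a within-study comparison for them.
- For any stated difference by age (prevalence or incidence) or by pregnancy (prevalence, as Section 3.6 limits it), estimate the prevalence ratio or rate ratio within each study that holds both categories and pool the ratios by random effects. Alternatively, fit a one-stage model with study intercepts and covariates centred on their study means. Report how many studies and women contribute to each contrast.
- Label period differences as between-study unless studies straddle a period boundary.
- Reconcile Section 5.2.1, which attaches the period to the study, with Section 3.6, which defines it from each woman's baseline data.

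The cost is wording and one more model per infection on the same data. Studies with only one category, such as Study 2 for age, drop out of the contrast but stay in the descriptive estimates.

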**5.2.1.a Heterogeneity Assessment**

Marked heterogeneity between studies may make it inappropriate to calculate overall summary measures of prevalence and incidence for each STI/BV, but exploring this heterogeneity can provide valuable insights. First, we will examine between-study heterogeneity in estimates of prevalence and incidence visually using forest plots of the summary estimates. We will use two statistics to measure the degree of heterogeneity in this meta-analysis: 1) the Q-statistic for which a p-value <0.10 will be interpreted as statistical evidence of heterogeneity (exceeding what would be expected by chance); 2) the I^2^ statistic and its 95% confidence interval, which describes the percentage of total variation across studies due to heterogeneity other than chance [26].

We will use the I^2^ statistic to classify the degree of between-study heterogeneity into low heterogeneity (I^2^ <50%), mild or moderate heterogeneity (I^2^ between 50-75%), and high heterogeneity (I^2^ > 75%). If we find low between-study heterogeneity, no further investigation of heterogeneity will be done. Otherwise, we will examine potential reasons for between-study heterogeneity using stratification or meta-regression. The outcome of this exploration of heterogeneity will determine decisions about the appropriateness of meta-analysis to pool the prevalence and incidence estimates from the component studies. If the decision is to pool the estimates, random-effect models will be used to incorporate the heterogeneity.

**5.2.2 One-stage meta-analysis**

The one-stage method combines and analyzes data from all studies as if they belong to a single study. Study identity is included in statistical models to take into account the fact that the data are from different studies. This can be seen as a multilevel model, with two levels, which allows the estimation of effects of interest in relation to both study-level and patient-level covariates. The one-stage method might not be a valid option if there is marked heterogeneity between the studies.

We will use stratified binomial regression model to examine overall prevalence estimates. We will use stratified Poisson regression to examine the overall incidence estimates. The impact of the over dispersion effects on the pooled prevalence and incidence estimates will also be evaluated.

**5.3. Study limitations and sensitivity analyses**

Though this meta-analysis provides high quality individual participant data and valuable information about the prevalence and incidence of selected STIs/BV, our approach has some limitations. First, the validity of the results of the meta-analysis is dependent on the quality of the individual component studies. While the IPD meta-analysis can help avoid problems associated with the analyses and reporting of the component studies, it cannot eliminate bias due to their study design or conduct. For example, studies which recruited high-risk women will likely have higher incidence estimates. In addition, due to the variety of study designs, not all stratification subgroups may be available in all component studies. Second, as the HC-HIV meta-analysis dataset is a convenience sample of prospective longitudinal studies that were identified for an analysis of hormonal contraception and the risk of HIV acquisition, the studies included may not be representative of all populations in the regions of interest for the STI/BV analysis. Finally, it is also possible that we may be unable to recode variables appropriately across studies and may not be able to investigate all sub-classifications of interest.

We will perform the following sensitivity analyses to examine the robustness of the results of our meta-analyses:

1. Based on the type of diagnostic criteria – stratify and analyze data/studies by the following criteria :
2. For chlamydia and gonorrhea: any test vs. NAAT only
3. For BV: any test vs. Nugent/Ison-Hay only
4. Based on the assessment of the risk of bias of the component study – stratify studies with and without an identified risk of bias. Suggested stratification for incidence estimates: studies that have retention rates <80% at one year vs. studies that have ≥80% retention
5. Based on intervention arm – repeat incidence analysis excluding all intervention arms.
6. Based on length of follow-up – for calculation of incidence, stratify studies with short versus longer follow-up time periods. Suggested stratification: ≤3 months vs 3 or more months followup
7. Based on study inclusion criteria – remove studies that included diagnosis with a specific STI for study inclusion for investigation of the prevalence and incidence of other STIs (if resources allow)
8. Based on censoring criteria – for calculation of incidence do not censor at first diagnosis of STI in question (if resources allow)

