  - - - Tested at least 80% of enrolled participants for the STI at follow-up or at least 80% of randomly selected participants as per protocol at follow-up
- Measured important covariates

The following types of studies in the HC-HIV meta-analysis dataset will be excluded:

- Where the study design required the STI diagnosis in question for study inclusion
- Where all participants received an STI prevention intervention likely to have an impact on STI incidence
- Where only symptomatic patients were tested on follow-up visits
- If >10% of those tested for the STI had indeterminate test results

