**3.8. Assessment of the risk of bias in individual studies**

All studies included in the HC-HIV meta-analysis dataset are cohort studies or randomized trials.

Knowledge of methodological features that can bias study results is important for interpreting the findings from individual studies and how the differences between studies might contribute to heterogeneity in study results. Unlike meta-analyses based on aggregated data, which generally rely only on information within published papers, an in-depth assessment of the risk of bias in individual studies will be possible. The assessment will make use of the individual participant data, study protocols, clinical study reports, available publications and communications with the study investigators. Additional factors can be assessed, such as whether those lost to follow-up were systematically different to those who remained in the study.

This process has already been completed for the HC-HIV IPD meta-analysis but will be revisited to include issues related to the assessment of STI prevalence and incidence. Using the study protocol, published articles and data sent by the studies, two reviewers will assess independently the following items (no score will be used) that has been adapted from the Strengthening the Reporting of Observational Studies (STROBE) statement and checklist:

For objectives 1 and 2:

1. How much data on STIs/BV are missing?
2. Were important covariates measured in the study?
3. Were appropriate STI/BV diagnostic tests used?

For objective 2:

1. Was the level of retention high in the study (>80% at 12 months)?
2. How frequently were STIs measured?

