| **To evaluate the prevalence/incidence of STIs/BV based on the assessment of the risk of bias** | **All studies** |  | **√** |  | **√** |
| **To evaluate the incidence of STIs/BV based on HIV diagnosis** | **All studies** |  | **√** |  | **√** |
| **To evaluate the incidence of STIs/BV based on length of follow-up** | **All studies** |  | **√** |  | **√** |
| **To evaluate the prevalence/incidence of STIs/BV based on the study inclusion** | **All studies** |  | **√** |  | **√** |
| **To evaluate the incidence of STIs/BV based on censoring** | **All studies** |  | **√** |  | **√** |

^1^ If the size of analysis population within each cross-stratum is sufficient to conduct the meta-analysis

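### Splitting whole studies at 80% retention cannot, on its own, show whether loss to follow-up biases incidence, and the lost-versus-retained comparison that section 3.8 says is possible is not committed to

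*Protocol*

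**What the plan says.** Protocol section 5.3, item 4, bases a sensitivity analysis on the risk-of-bias assessment: "stratify studies with and without an identified risk of bias. Suggested stratification for incidence estimates", followed by "studies that have retention rates <80% at one year vs. studies that have ≥80% retention". The cut is offered as a suggestion, but the unit is the study whatever cut is used. The matching row of Table 5, "To evaluate the prevalence/incidence of STIs/BV based on the assessment of the risk of bias", has all studies as its analysis population and shows no population-type or region strata.

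The limitations paragraph of section 5.3 states that "studies which recruited high-risk women will likely have higher incidence estimates".

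Section 3.8 says individual data permit a fuller assessment: "Additional factors can be assessed, such as whether those lost to follow-up were systematically different to those who remained in the study". The items it then lists for objective 2 are only the retention level (above 80% at 12 months) and how often STIs were measured.

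Section 3.5 censors at the last visit with STI testing and states no adjustment for loss. Section 5.2.1 pools estimates by population type. Section 3.2 admits a study to the incidence analysis only if it "Tested at least 80% of enrolled participants for the STI at follow-up or at least 80% of randomly selected participants as per protocol at follow-up".

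**The concern.** Loss to follow-up biases an incidence rate when the women who leave have a different rate from those who stay. That is a question about women within a study. Item 4 compares different studies, which may differ in who was recruited, where, when and with which assay. The protocol itself expects recruitment to affect incidence.

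A difference between the retention strata therefore need not come from loss, and similar strata do not show that loss is harmless. Incidence is a primary objective, and the check bears on how far its estimates can be trusted. Individual records would allow a more direct look, but no planned analysis uses them for this.

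**Working it through.** **Step 1. Figures in the plan.** The protocol gives no retention, incidence rate or sample size for this check. The one related total is about 37,000 women. The Table 1 column sums to 37,681 (1.8% above), so it reproduces. By category:
- clinic/community: 15 rows, 29,890 women (9 rows South Africa, 4 Southern Africa, 2 Eastern Africa)
- high-risk: 7 rows, 5,752 women, all Eastern Africa
- HIV-discordant couples: 4 rows, 2,039 women

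For the high-risk rows, population type and region cannot be separated. All rates and proportions below are assumptions.

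**Step 2. Study mix alone, no loss bias.** Let R be the rate in high-risk studies relative to the others, and a and b the share of high-risk studies in the low- and high-retention strata. The low/high ratio is [1 + a(R−1)] / [1 + b(R−1)].

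| R | a = 0.6, b = 0.1 | a = 0.1, b = 0.6 |
|---|---|---|
| 1.5 | 1.30/1.05 = 1.24 | 1.05/1.30 = 0.81 |
| 2 | 1.6/1.1 = 1.45 | 1.1/1.6 = 0.69 |
| 3 | 2.2/1.2 = 1.83 | 1.2/2.2 = 0.55 |

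**Step 3. Loss bias within one study.** Let d be the proportion lost, k the rate in lost women relative to retained women, and h the fraction of the year that lost women contribute. Observed over true rate is {[(1−d) + dhk] / [(1−d) + dh]} / [(1−d) + dk].

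Take d = 0.20 with lost women contributing 10% of person-time, which gives h = 0.08/0.18 = 0.44:
- k = 1.5: (0.9 + 0.1×1.5)/(0.8 + 0.2×1.5) = 1.05/1.10 = 0.955, or 4.5% too low
- k = 2: (0.9 + 0.1×2)/(0.8 + 0.2×2) = 1.10/1.20 = 0.917, or 8.3% too low

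If lost women had the lower rate, the sign would reverse. At d = 0.30 and k = 0.67, the rate is 4.5% too high with h = 0.5 and 11% too high with h = 0.

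**Step 4. What the split would see of that bias.** The ratio of step 3 in a low-retention study to step 3 in a high-retention study is, for h = 0 and h = 0.5:
- 30% against 10% lost, k = 1.5: 0.91 and 0.97
- 30% against 10% lost, k = 2: 0.769/0.909 = 0.85 and 0.905/0.957 = 0.95
- 21% against 19% lost, k = 2: 0.98 and 0.99

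These lie inside the range that study mix alone can produce in step 2. The high-retention stratum is not a clean reference either: at 10% lost and k = 2 its rate is already 4-9% low.

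**Step 5. Simulation.** This used all 26 rows of Table 1 and 1,000 runs, with R = 2, 8 per 100 woman-years, between-study SD 0.3 on the log rate, and 30% or 10% lost. A measured baseline factor in 30% of women raises loss 1.8-fold and multiplies the rate by k. The share of high-risk studies with low retention was 10%, 30% or 70%.

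| | Split: median low/high ratio | Split: 95% range over the three | Within study, observed/standardised: medians (95% range) |
|---|---|---|---|
| k = 1 (no bias) | 0.86, 1.01, 1.27 | 0.58-1.84 | 1.00 (0.99-1.01) |
| k = 2 | 0.81, 0.93, 1.21 | 0.55-1.67 | 0.96-0.97 (0.94-0.98) |

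The split looks much the same with and without bias, while the within-study comparison separates them. It does so only because the factor that drives loss is measured. Fewer than 26 rows would enter the real incidence analysis, so its precision would be lower than shown.

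**Step 6. The text.** Section 3.8 names the lost-versus-retained comparison as possible. It is absent from that section's list of items, from section 5.3 and from Table 5.

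**The case against.** Several points on the other side stand.

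- **The split is modest in intent.** The 80% cut is only suggested. Item 4 examines robustness and does not promise to estimate or exclude loss bias. The protocol also commits to cautious interpretation. A reader might infer that the authors will blame retention for a population difference, or declare incidence robust; the text supports neither prediction.
- **The all-studies label does not prove that population types are mixed.** Table 5 gives the co-infection rows the same label, yet section 3.7 estimates co-infection by population type. Section 5.2.1 pools by population type, section 3.6 plans cross-stratification where numbers allow, and section 5.2.1.a provides stratification or meta-regression. The plan does not say whether item 4 follows these. Splitting within population type would reduce the confounding, but region, period and assay would remain and few studies would be left per cell.
- **The 80%-tested criterion in section 3.2 may leave few studies below 80% retention**, depending on how follow-up is read there. No particular division of studies between the strata can be assumed.
- **Modelling detail can sit in the SAP**, which is not at hand. This holds for the form of the weights. It does not answer the point that the protocol names a specific check that cannot separate loss from study mix.
- **Within-study analysis has limits.** Rates before loss do not reveal rates after it. Women later lost contribute only early person-time, so adjusting for age alone is not enough. Weights address only measured reasons for leaving.

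**Conclusion.** The point holds in a limited form. On its own, the suggested study-level split cannot show whether loss biases incidence, because study mix can produce ratios as large as or larger than those from loss, in either direction. The protocol does not commit to the comparison that its own section 3.8 says individual data allow.

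The size is uncertain and probably modest: about 4.5-8% understatement if 20% are lost, contribute about 10% of person-time and have 1.5 to 2 times the rate. A reader might infer 9-17%, from 1 − 1/1.1 and 1 − 1/1.2. That requires lost women to contribute no person-time at all, which the documents do not support as the general case. Nor do they show that the primary incidence estimates are in fact biased, since no study's retention is reported. This is an inexpensive improvement to a sensitivity analysis.

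**What to change.** 1. Show the 80% split within population type and label it descriptive. Use one boundary: section 3.8 has above 80%, section 5.3 has 80% or more.
2. In each study, compare baseline factors between lost and retained women: age, condom use, number of partners, and baseline STI results where available. If rates before loss are also compared, adjust for time in study as well as age.
3. As a sensitivity analysis, re-estimate each study's incidence for each STI with inverse-probability-of-censoring weights, or standardisation, on those factors. Pool as in the main analysis within population type and report the change from the main estimate.
4. Add items 2 and 3 to the risk-of-bias row of Table 5.

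Cost: revised wording and one weighting model per study and STI, because the criteria in section 3.2 apply to each STI separately and section 3.5 censors at the last STI test. Age, condom use and number of partners were required of every study (Table 2); baseline STI results were not. The correction covers only measured predictors of loss, and women lost before their first follow-up test supply no outcome information.
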